### Demographics and individual differences

Information about demographics and individual differences will also be collected at time point 1. This includes age, biological sex (man, female, inter-sex, prefer not to say), gender (man, woman, non-binary/non-conforming, trans-gender, prefer not to say), nationality, and education. High sensitivity will be measured using the English translation of the validated Dutch short version of the newly developed Sensory Processing Sensitivity Questionnaire – Short Form (SPSQ-SF), consisting of 26 items (SPSQ-SF) [13]. A total score can be formed in addition to six subscales: (1) Sensory Sensitivity to Subtle Internal and External Stimuli, (2) Sensory Comfort, (3) Social-Affective Sensitivity, (4) Aesthetic Sensitivity, (5) Emotional and Physiological Reactivity, and (6) Sensory Discomfort. The first four subscales load onto a positive SPS dimension, whereas the last two load onto a negative SPS dimension [53]. The items are assessed on a seven-point Likert scale (1-7), sum scored together.

Furthermore, two bespoke questions will be asked to evaluate participants’ past experience with the arts, including interest and engagement: “How interested are you in art, music, or visiting art/cultural spaces? (1 not at all, 7, very much)”; second, “In the past year, how often have you engaged with/attended/visited arts venues (including music events, the theatre/dance, concerts, art museums, art festivals, exhibitions, either in-person or online, etc.)? 1) More than once a month, 2) once a month, 3) once every two or three months, 4) three times per year, 5) twice per year, 6) once a year, 7) not in the past year.” These two questions will then be summed together and treated as a continuous variable. These questions are based on the art interest construct from the widely used Vienna Art Interest and Knowledge scale [54]. Finally, openness to experience will be measured with the openness facet of the Big Five Inventory (BFI; [55]), which has ten questions. These questions are measured on a 1 to 5 Likert scale (strongly agree to strongly disagree) and will be summed together.

### Expectation, credibility, adherence, and enjoyment

To understand how participants’ expectations and adherence might impact the results of the trial, several aspects will be assessed at time point 1. Expectation and credibility will be measured through the Credibility and Expectancy Questionnaire (CEQ), which has six questions about how much participants expect the programme to benefit their well-being [56]. We have slightly modified this questionnaire from its intended use as a clinical instrument for therapies, asking about improvement in functioning by replacing the term “functioning” with “well-being” in the questions.

To measure adherence, as part of the programme, each day, participants will also be asked to indicate whether they fully, partially or did not complete the programme elements for that day. These questions were introduced in the enrollment meeting with emphasis on the need for honesty that would not impact any compensation. Adherence will also be monitored via the number of sign-ins and their progress in the online programmes. Finally, enjoyment of the programmes will be assessed on a 1–7 Likert scale.

### Qualitative interview

A semi-structured qualitative interview after timepoint 3 will be conducted with a subset of participants focusing on the effects and learning outcomes of the intervention and control programmes, mechanisms, barriers and facilitators. We will follow the Consolidated Criteria for Reporting Qualitative Research (COREQ; [57]).

### Participant timeline {13}

#### Enrollment and baseline

In an enrollment meeting hosted on Microsoft Teams, the researcher will walk the participant through the selected programme components and instructions with a PowerPoint presentation and provide time for questions. As listed in the information sheet, advertisement, and screening survey, the participants will be asked for their postal address so that the login details for the respective programme and the free museum tickets (intervention only) can be sent via post. Participants will set up an account on the Samply Research Application [58] to receive reminders about the study. At the end of the meeting, the researcher will explain that the surveys will be sent to them via email (via Castor). Once the participant has no further questions, the enrollment meeting will finish. The participants will then be sent the baseline survey. The list of baseline questions is provided in the overview in Table 3.

**Table 3 Tab3:** Outcomes and timepoints of assessment

Assessment tools	Baseline T1	Post T2	Follow-up T3

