### Intervention and control programmes

After finishing the baseline survey and the research materials arrive by post, the participant can access the online programme platform (hosted on Thinkific, an online course-sharing platform) to start the programme. The programme is followed daily for 14 days by logging into Thinkific on their personal phones or computers (see Intervention section for intervention procedure description).

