### Implementation {16c}

The enrollment researchers will assign participants to conditions during the enrollment meeting, after informed consent, using the automatic randomisation sequence generated by Castor.

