## Assignment of interventions: blinding

### Who will be blinded {17a}

Participants are blinded to the allocated condition. Although the information sheet specifies that there are two conditions, it is unclear to participants which is the control and which is the intervention due to the high-quality, credible active control condition. It is not possible in this study to keep the researchers blind, as they are responsible for explaining the programmes during the enrollment meeting.

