### Plans to promote participant retention and complete follow-up {18b}

Participants are informed of their right to leave the study at any time without consequences to themselves. Reasons for withdrawals and timing will be documented. To promote participant retention, we will send reminders to those who stop having poor adherence and ask all withdrawn participants to complete the post and follow-up tests where possible. Participants who withdraw are not replaced if they have completed the pre-survey.

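### Baseline scales are collected after allocation and programme briefing, so the ANCOVA covariate and the SPS moderator are open to arm-specific reporting

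*Protocol article*

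**What the plan says.** Four sections of the protocol article fix the order of events.

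- Implementation {16c}: "The enrollment researchers will assign participants to conditions during the enrollment meeting, after informed consent".
- Enrollment and baseline: in that meeting "the researcher will walk the participant through the selected programme components and instructions with a PowerPoint presentation". Postal addresses are also requested so that "the login details for the respective programme and the free museum tickets (intervention only) can be sent via post".
- Who will be blinded {17a}: researchers cannot be blind because "they are responsible for explaining the programmes during the enrollment meeting".
- Enrollment and baseline, on the survey: "Once the participant has no further questions, the enrollment meeting will finish. The participants will then be sent the baseline survey".

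The programme itself starts later still: "After finishing the baseline survey and the research materials arrive by post, the participant can access the online programme platform" (Intervention and control programmes).

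Table 3 places the EBS-R, MHC-SF, DASS-21, SPSQ-SF and CEQ in the T1 survey. Section {20a} uses baseline scores, sex and age as ANCOVA covariates. Section {20b} uses pre-post change for the Reliable Change Index (RCI) and SPS as moderator. On replacement, section {18b} says: "Participants who withdraw are not replaced if they have completed the pre-survey". Section {20c} makes availability of pre- and post-data a condition for the ITT analysis.

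**The concern.** Adjusting for a baseline score is safe in a randomised trial because allocation cannot have influenced the score. Here it can. The participant has been allocated and briefed before answering, and the covariate is a self-report.

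The EBS-R is the most exposed scale. The Recruitment section keeps art and beauty out of the advertisement, and only the intervention arm is sent museum tickets. The two arms may therefore approach a questionnaire on engagement with artistic and natural beauty in different frames of mind. Any resulting difference enters the primary estimate through the covariate, the RCI through the pre-score, and the exploratory moderation through the SPSQ-SF, which has an aesthetic sensitivity subscale.

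The same order has a second consequence. Anyone who leaves between allocation and the survey is a randomised participant without a baseline score.

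**Working it through.** **1. Order of events.** Taken together, the sections give: consent, allocation and programme explanation within the meeting, end of meeting, T1 survey, programme access. No section places T1 before randomisation. The CEQ points the same way: it is a T1 measure and asks what benefit is expected from the programme, so the programme must already be known.

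**2. Inputs.** From Sample size {14}: pre-post correlation r = 0.72, planned d = 0.35 and 49 per group before dropout. The design factor reproduces: 1 - 0.72² = 0.4816, given as 0.48. The residual SD is √0.4816 = 0.694. The shift s is not in the documents. The values 0.1 and 0.2 SD are assumptions for illustration, as is equal SD at T1 and T2, which makes the slope 0.72.

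**3. Bias formula.** The ANCOVA effect is the T2 difference minus 0.72 times the T1 difference. Let the true effect be τ and the allocation-induced T1 shift in the intervention arm be s.

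- Shift gone by T2: τ - 0.72s.
- Same shift still present at T2: τ + s - 0.72s = τ + 0.28s.
- No shift: τ.

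| s (assumed) | Bias, shift gone by T2 | Share of 0.35 | Bias, shift persists | Share of 0.35 |
|---|---|---|---|---|
| 0 | 0 | 0% | 0 | 0% |
| 0.1 | -0.072 | 21% | +0.028 | 8% |
| 0.2 | -0.144 | 41% | +0.056 | 16% |

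A negative s reverses every sign. In the RCI, a shift gone by T2 enters the change score in full (-s), and a persisting one cancels.

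**4. Effect on the test, shift gone by T2, 49 per group, two-sided 5%.** The standard error is 0.694 × √(2/49) = 0.140. With no true effect, s = 0.1 displaces the test statistic by 0.072/0.140 = 0.51 and raises the type I error to about 8%. At s = 0.2 it is about 18%. With a true effect of 0.35, two-sided power falls from about 70% to 51% (s = 0.1) or 31% (s = 0.2). The starting value is 70% and not 80% because 102 per group before the design factor corresponds to a one-sided test. That is a separate matter and does not bear on this point.

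**5. Analysis without the baseline score.** 0.35/√(2/49) = 1.73, and 1.73 - 1.96 = -0.23, so two-sided power is about 40% at 49 per group. At 57 per group it is about 46%.

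**6. Losses after randomisation.** A person allocated in the meeting who never completes the survey has no baseline score. Carrying the last observation forward cannot supply one, so the ANCOVA cannot use that person. Because the survey follows allocation, this is a post-randomisation exclusion that could differ by arm. Section {18b} rules out replacement only for those who completed the pre-survey and is silent on the others.

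**The case against.** The best defence is that the order is shown but harm is not.

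- **Briefing content.** The slides are not shown. A reader might infer that intervention participants are told they will learn to appreciate beauty. The documents do not say so: they speak of programme components and instructions, and the study is promoted as an observation programme. The museum tickets make it likely that this arm hears of a museum visit, but no more than that is documented.
- **Blinding and timing.** Participants do not know which programme is the control, and no programme activity precedes T1. This rules out contamination by the activities, but not by the briefing.
- **Trait scale.** The Outcomes section presents the EBS-R as a trait measure. That makes a large shift less likely. It does not make self-report immune.
- **Persistence.** If the shift lasted to T2, the present order would leave +0.28s in the estimate, whereas a pre-allocation baseline would leave the whole of s. Moving the survey therefore protects the covariate but does not remove reporting differences at T2. This stands and limits what the fix can claim.
- **Moderator.** H4 is exploratory, and SPS is treated as a trait. The timing weakens the moderation analysis but does not invalidate it.
- **Replacement.** A reader might infer that early leavers are removed and replaced. Section {18b} does not say that, and adding a participant does not delete another. The loss of people without pre-data comes from {20c} and from the missing covariate. What stands is that {18b} leaves replacement open.

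**Conclusion.** The concern holds as a design weakness of unknown size. The covariates for the primary and secondary ANCOVAs, the RCI pre-scores and the exploratory SPS moderator are all post-allocation self-reports, although they precede the programme. Age and sex are not affected.

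The documents do not show that any result is biased, and they do not fix the direction. The figures of 0.07 and 0.14 SD rest on assumed shifts of 0.1 and 0.2 SD that vanish by T2. Under persistence they become 0.03 and 0.06 SD with the opposite sign, and without a shift they are zero. The post-randomisation loss of people without a baseline score needs no assumption about reporting, but its number and any imbalance between arms are not documented.

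**What to change.** **Remaining enrollees.** Have all T1 scales except the CEQ completed after consent and before Castor releases the allocation and any programme is explained. Keep the CEQ after the briefing. State in {18b} and {20c} that every randomised participant stays in the ITT accounting and none is replaced.

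**Participants already enrolled** (recruitment began in November 2024). Report the order of events, show baseline means by arm, and add a T2 sensitivity analysis without the baseline score. State that its power is only about 40% at 49 per group for d = 0.35, so it cannot settle whether a bias of 0.07 SD exists. Baseline means by arm cannot separate a reporting shift from chance imbalance either.

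**Cost.** The sample size is unchanged. By the item counts in Table 3 the T1 survey has 160 items, so 160 - 6 = 154 would fall between consent and allocation. That means a longer step before allocation and possibly a split meeting. Because recruitment was planned to end in June 2025, only later enrollees benefit from the change in order.

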**Demographics and covariates**			
Demographics (6 items)	x		
SPSQ-SF (26 items)	x		
Experience with Arts (bespoke; 2 items)	x		
BFI-O (10 items)	x		
**Primary outcome**			
EBS-R (18 items)	x	x	x
**Secondary outcomes**			
MHC-SF (14 items)	x	x	x
DASS-21 (21 items)	x	x	x
**Tertiary outcomes**			
ERS-ACA (18 items)	x	x	x
Beauty Awareness Question (1 item)		x	x
FFMQ-15 (15 items)	x	x	x
ACS-12 (12 items)	x	x	x
BAT-12 (12 items)	x	x	x
Interview*			x
**Additional questions**			
CEQ (6 items)	x		
Adherence and Enjoyment (2 items)		x	
Additional background questions (2 items)			x

*SPSQ-26 *Sensory Processing Sensitivity, *BFI-O* Big Five Inventory-Openness, *EBS-R* Engagement with Beauty Revised, *MHC-SF* Mental Health Continuum Short Form, *DASS-21* Depression, Anxiety, and Stress Scale-21 item, *ERS-ACA* Emotion Regulation Strategies for Artistic Creative Activities Scale, *FFMQ-15* Five Facets Mindfulness Questionnaire Short Form, *ACS-12* Attention Control Scale-12 item, *BAT-12* Burnout Assessment Tool-12 item, *CEQ* Credibility and Expectancy Questionnaire. *Interviews will only be conducted in a subsample (*n* = 25) until data saturation

### Intervention and control programmes

After finishing the baseline survey and the research materials arrive by post, the participant can access the online programme platform (hosted on Thinkific, an online course-sharing platform) to start the programme. The programme is followed daily for 14 days by logging into Thinkific on their personal phones or computers (see Intervention section for intervention procedure description).

### Post-survey, follow-up survey and compensation

The post-survey will be sent once participants have completed the 14-day programme. The list of surveys is in Table 3. At this time, participants are reminded that in 4 weeks, they will be sent the final survey and, following its completion, their compensation. Once the participant has completed it, as confirmed by checking the ID codes of the completed surveys, they will be awarded their Dutch online shopping voucher (Bol.com) and research credits.

### Semi-structured qualitative Interviews

After follow-up (4 weeks post-intervention), participants selected through purposive sampling (selecting to maximise diversity by varying levels of programme completion, gender, age, and level of SPS) will be sent an invitation to participate in a qualitative interview with the information sheet and the interview-specific informed consent sheet. The interviews will be conducted one-on-one by one of the study’s researchers on Microsoft Teams, which allows recording and automatic transcription. Transcripts will be sent to interviewees to check all is correct. Participants will be compensated with an online shopping voucher. The interview description can be found in the Outcomes Section.

**Fig. 1 Fig1:**
[figure not shown]
Participant timeline

For the qualitative interviews, as is common in qualitative research, it is not yet possible to determine how many participants will participate in the interviews. Participants will continue to be approached and interviewed until the interviews no longer generate new information (i.e. data saturation is reached). The point at which saturation occurs depends, among other factors, on the heterogeneity of the sample. Given that our sample is relatively homogeneous (mostly university students and young adults in Amsterdam), we anticipate that a sample of approximately *N* = 20 participants will ultimately be included, *N* = 10 per group. An additional *N* = 5 high SPS individuals from the intervention group will be selected for a subgroup analysis. If participants do not accept the invitation, we will contact replacements from the remaining pool of intervention condition participants.

### Recruitment {15}

Participants will be recruited through the participant platform at the University of Amsterdam and via social media. The participant platform advertises studies to students and provides them with research credits they must complete as part of their undergraduate curriculum. An advertisement will be placed on the participant platform that includes necessary study information with a link for interested participants to click to fill out a screening survey (via online survey platform Qualtrics, https://www.qualtrics.com) and provide their contact email. This survey starts with the information letter and a screening informed consent. The intervention and control programmes will be advertised as targeting observation skills while being a tourist in your city. There is no mention of art or beauty appreciation in the advert. In addition, advertisements will be placed on social media with links to the study information and the same screening survey.

## Assignment of interventions: allocation

### Sequence generation {16a}

Participants will be randomised in blocks of 2 and 4 via a sequence generated by the electronic data capture system Castor (https://www.castoredc.com).

### Concealment mechanism {16b}

The sequence for randomisation is concealed from researchers within Castor. Further, using blocks of 2 and 4 reduces the possibility of guessing the next condition.

### Implementation {16c}

The enrollment researchers will assign participants to conditions during the enrollment meeting, after informed consent, using the automatic randomisation sequence generated by Castor.

## Assignment of interventions: blinding

### Who will be blinded {17a}

Participants are blinded to the allocated condition. Although the information sheet specifies that there are two conditions, it is unclear to participants which is the control and which is the intervention due to the high-quality, credible active control condition. It is not possible in this study to keep the researchers blind, as they are responsible for explaining the programmes during the enrollment meeting.

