## Statistical methods

### Statistical methods for primary and secondary outcomes {20a}

The main analysis will be conducted in two stages. The first is according to the intention-to-treat (ITT) analysis principle [60], with all participants included where possible. This includes dropouts and non-completers of the programmes. Second, we will repeat the analysis Per-Protocol (PP) [60] to gain a clearer picture of the intervention-related effects, excluding non-completers or poor-quality data (see exclusions below). To evaluate whether there are differences between the conditions at the post-test, considering baseline differences, a series of ANCOVAs with the condition as the IV and the post-test as the DV, with baseline scores, sex, and age as covariates will be run on primary and secondary outcomes. To evaluate the long-term effects of the intervention and the control condition, linear mixed models (LMM) will be fitted to predict each outcome variable. The same approach will be applied to evaluate the tertiary outcomes.

For more details, see our pre-registration: osf.io/q8c6u.

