### Methods in analysis to handle protocol non-adherence and any statistical methods to handle missing data {20c}

In ITT analysis, we will only exclude participants who do not have pre- and post-data for the DV in question. We will record reasons for dropout and look at baseline measures between groups to assess the randomness of missing data. If data are found to be random, missing outcome data will be used as the last observation carried forward approach [62]. In PP analysis, participants will be excluded if they a) fail two out of three of the attention of the checks (1 per survey), b) signed into the programme less than seven times or c) self-reported not completing more than seven activities, indicating they have done less than half of the programme (for more details see the pre-registration).

The qualitative data will be analysed using thematic analysis within the qualitative software package Atlas.ti (version 24.1.1), employing a constant comparison method and adhering to the framework of Braun and Clarke [40], utilising open coding [63]. Two researchers will code the transcripts (a PhD candidate and an MSc level researcher). The first five transcripts will be independently coded by both coders and subsequently compared, while the remaining transcripts will be coded by one researcher and checked by the other. Mapping the codes involves examining the transcript, coding, grouping codes into themes and subthemes, and identifying the core concept through axial and selective coding [63, 64], moving back and forth between the codes and the original data [64]. The coders will meet regularly to discuss the codes and emerging patterns, as well as to assess when data saturation has been achieved.

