## Oversight and monitoring

### Composition of the coordinating centre and trial steering committee {5d}

The coordinating centre comprises the principal investigator, the lead researcher, and other personnel. The principal investigator oversees the scope of the experiment, while the lead researcher manages the daily operations and research team, including recruitment, enrollment, data collection, monitoring, analysis and reporting. Weekly meetings occur between the lead researcher and the research personnel and bi-weekly meetings are held between the entire team to track progress. Emergency meetings are convened as necessary. There is no involvement from a steering committee or stakeholders.

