### Composition of the data monitoring committee, its role and reporting structure {21a}

There is no monitoring committee; the research team conducts the monitoring.

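### The reason given for leaving researchers unblinded covers enrolment only; the quantitative analysis could be done on coded arms at little cost

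*Protocol article*

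**What the plan says.** On blinding, section {17a} of the protocol article states two things: "Participants are blinded to the allocated condition", and "It is not possible in this study to keep the researchers blind, as they are responsible for explaining the programmes during the enrollment meeting". Section {16c} shows where allocation becomes known to staff: "The enrollment researchers will assign participants to conditions during the enrollment meeting, after informed consent".

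On roles, section {5d} says that "the lead researcher manages the daily operations and research team, including recruitment, enrollment, data collection, monitoring, analysis and reporting", and that there is no steering committee. Section {21a} adds: "There is no monitoring committee; the research team conducts the monitoring". No section names a separate analyst or describes coded arm labels.

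On analysis decisions:
- Section {20a} fixes the main ANCOVA covariates as baseline score, sex and age. It describes the second-stage per-protocol analysis as "excluding non-completers or poor-quality data (see exclusions below").
- Section {20c} gives the per-protocol limits: two of the three attention checks failed, or "signed into the programme less than seven times or c) self-reported not completing more than seven activities".
- Section {20c} also says that the team will "look at baseline measures between groups to assess the randomness of missing data". If the data are judged random, LOCF is applied.
- Section {20b} adds a scale as an exploratory covariate when the groups differ significantly on it.

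Sections {20a} and {20c} refer to a pre-registration for further detail.

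**The concern.** The article takes a position on researcher blinding and gives a reason for it. The reason is sound for the people who allocate participants and talk them through their programme. It says nothing about work on an exported file, where arm labels can be replaced by codes. Because {17a} speaks of the researchers without limit, and {5d} puts enrolment, monitoring and analysis under one role, the text can be read as accepting an unmasked analysis by default.

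What is at stake is modest but specific. Where a rule needs interpretation once the data are in, knowing which arm is which can colour that interpretation, even without intent. The same team developed the intervention, and the planned effect is small to moderate (d = 0.35). The Discussion counts support for blinding among the design's strengths, so an avoidable gap at the analysis stage weakens a claim that the authors make themselves.

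**Working it through.** The article gives no figure on this point to reproduce. The check compares the stated reason with each task, then sorts the analysis decisions into fixed and open.

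**1. Does the stated reason reach the task?**

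| Task | Section | Does explaining the programmes at enrolment require knowing the arm here? |
|---|---|---|
| Allocation and programme briefing | {16c}, {17a} | Yes |
| Reminders and technical support to non-adherers | {11c} | The given reason does not cover it, but supporting a programme plainly reveals it |
| Quantitative outcome collection | {18a} | No; participants complete surveys in Castor and no researcher rates them |
| Exclusions, missing-data decision, models | {20a} to {20c} | No |
| Interview coding | {20c} | Not for that reason, but the transcripts themselves would disclose the arm |

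The reason fails for the fourth row, and that is the row where masking is practicable.

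**2. Which analysis decisions are open?**

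*Fixed:* the main ANCOVA covariates; the numeric per-protocol limits; the exploratory status of any added covariate.

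*Open in the primary analysis:*
- {20c} states no criterion for judging missing data to be random, and does not say what happens if they are not.
- {20c} drops from the intention-to-treat set anyone lacking baseline or post-test data on the outcome, yet also carries observations forward. A participant with a baseline score and no post-test score is excluded under the first rule and could be imputed under the second. One reading reconciles them (LOCF for the follow-up only), but the text does not say so.

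*Open to a lesser degree:*
- Section {12} records each day's activities as fully, partly or not completed, while the per-protocol rule counts activities not completed. How a partly done activity counts is not stated.
- {20b} sets no significance level for adding a covariate.

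**3. How many participants could the open primary rule touch?** Inputs from section {14}: 49 per group needed, total 114.
- Needed in total: 2 × 49 = 98.
- Dropout allowance: 114 − 98 = 16, and 16/114 = 14.0%.

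If dropout runs as planned and those participants lack the post-test, the handling of about 16 people is in question.

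**4. Is an added covariate a realistic event?** Assume tests at 0.05 and independent scales (the article gives neither). The factors in {20b} come to roughly 4 to 6 scales, depending on how they are counted. The chance of at least one difference by chance is 1 − 0.95^k:
- k = 4: 18.5%
- k = 5: 22.6%
- k = 6: 26.5%

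**5. Can the bias be sized?** With r = 0.72 and 49 per group, SE = sqrt(2 × (1 − 0.72²)/49) = sqrt(2 × 0.4816/49) = 0.140 SD, so the planned effect sits at z = 0.35/0.140 = 2.5. A shift of 0.05 SD would move z by 0.05/0.140 = 0.36. The 0.05 is an arbitrary unit: nothing in the article ties any decision to a shift of that or any other size. The conversion shows the scale only and does not estimate bias.

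**The case against.** The strongest reply has four parts.

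- **The article is condensed.** Analyst masking is often set out in an analysis plan, and the pre-registration is not shown. This stands for the details: it may already define the missing-data criterion and the mixed model, and their absence here is not held against the plan. It does not rescue {17a}, which makes a general statement on a reason that supports only part of it.
- **A reader might infer that the lead researcher personally meets participants and then fits every model with the arms in view.** The article does not say so. Section {5d} says that this role manages those activities, and {16c} refers to enrolment researchers. This part stands; the point is only that nothing in the article separates or masks the analysis.
- **A reader might also infer wide freedom over exclusions and covariates.** That is not supported. The per-protocol limits are numeric, the mention of poor-quality data points to those limits, per-protocol is the second analysis, the main covariates are fixed, and added ones are exploratory. Self-report also removes researcher scoring of the quantitative outcomes as a route for bias.
- **Stating a criterion would do more than masking.** This is true for the randomness judgement: coded arms do not supply a missing rule. The two measures complement each other, since masking protects whatever judgement remains. The lack of monitoring and steering committees has no direct bearing on coding the arms.

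**Conclusion.** The concern holds in a limited form. The reason in {17a} does not justify leaving the quantitative analysis unmasked, and the article places that analysis under a role that also manages enrolment and monitoring. The exposure is narrow. It lies mainly in the missing-data judgement and the intention-to-treat exclusions, which at planned dropout concern about 16 of 114 participants, and to a lesser degree in partly completed activities and exploratory covariates.

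The documents do not show that any decision will be made with labels visible, nor that a result would be biased. The amount of bias cannot be computed.

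The conclusion assumes that the term researchers in {17a} covers the whole team, as it is worded, and that the pre-registration does not already provide for coded arms. If it does, only the wording of {17a} needs correcting. This is a cheap improvement, not a flaw that threatens the trial.

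**What to change.** 1. In {17a}, limit the statement that blinding is not possible to enrolment and programme-support staff.
2. State that the quantitative analysis is done on a locked Castor export with new participant codes and arms labelled A/B. Remove fields that reveal the programme, but keep sign-in counts, activity completion and attention checks in arm-neutral form, because the per-protocol limits need them.
3. On that file, settle exclusions, missing-data handling and covariates first, since a clear result could suggest which arm is which. Then run the primary and secondary models, archive the decisions and output with a time stamp, and only then unmask. A team member who does not run the analysis holds the key.

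Cost: one recoded export, a few sentences and a short delay before unmasking. No new staff are needed, and sample size, alpha and participant procedures do not change.

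Limits: in a small team that follows up individual non-completers, masking will be partial. It does not extend to the interview transcripts.
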